## Abstract

**Introduction:**

WHO recommends the use of pneumococcal conjugate vaccine (PCV) as a priority. However, there are many countries yet to introduce PCV, especially in Asia. This trial aims to evaluate different PCV schedules and to provide a head-to-head comparison of PCV10 and PCV13 in order to generate evidence to assist with decisions regarding PCV introduction. Schedules will be compared in relation to their immunogenicity and impact on nasopharyngeal carriage of *Streptococcus pneumoniae* and *Haemophilus influenzae*.

**Methods and analysis:**

This randomised, single-blind controlled trial involves 1200 infants recruited at 2 months of age to one of six infant PCV schedules: PCV10 in a 3+1, 3+0, 2+1 or two-dose schedule; PCV13 in a 2+1 schedule; and controls that receive two doses of PCV10 and 18 and 24 months. An additional control group of 200 children is recruited at 18 months that receive one dose of PCV10 at 24 months. All participants are followed up until 24 months of age. The primary outcome is the post-primary series immunogenicity, expressed as the proportions of participants with serotype-specific antibody levels ≥0.35 µg/mL for each serotype in PCV10.

**Ethics and dissemination:**

Ethical approval has been obtained from the Human Research Ethics Committee of the Northern Territory Department of Health and Menzies School of Health Research (EC00153) and the Vietnam Ministry of Health Ethics Committee. The results, interpretation and conclusions will be presented to parents and guardians, at national and international conferences, and published in peer-reviewed open access journals.

**Trial registration number:**

NCT01953510; Pre-results.

Strengths and limitations of this studyThis study is specifically designed to address two independent questions within a single study: which schedule to use for the provision of pneumococcal conjugate vaccine (PCV), and which PCV to use.This study includes a head-to-head comparison of the two licensed PCVs, allowing a direct assessment of their relative immunogenicity and impact on nasopharyngeal carriage.The primary outcome is the criteria used for the licensing and varying of PCV schedules.This study has relatively low power for the secondary nasopharyngeal carriage outcomes, so the ability to draw conclusions relating to these outcomes is vulnerable in the event of lower-than-anticipated carriage rates.

## Introduction

### Background and rationale

*Streptococcus pneumoniae* (pneumococcus) remains a leading vaccine preventable cause of serious infection in young children, despite the availability of effective vaccines. The first infant pneumococcal vaccine, the 7-valent pneumococcal conjugate vaccine (PCV7), was licensed in the USA in the year 2000. Introduction of PCV7 has been associated with dramatic reductions in pneumococcal disease.^1–3^ However, geographical variation in serotype distribution^4–7^ and an increase in invasive pneumococcal disease (IPD) caused by non-PCV7 serotypes following vaccine introduction^8^ necessitated the development of higher valency PCVs.

There are currently two licensed PCVs: PCV10, a 10-valent pneumococcal vaccine that uses non-typeable *Haemophilus influenzae* (NTHi) protein D as a carrier protein for 8 of the 10 serotypes (*Synflorix*, PHiD-CV; GSK); and PCV13, a 13-valent pneumococcal CRM_197_ conjugate vaccine (*Prevnar-13/Prevenar-13*; Pfizer). Both have been shown to be non-inferior to PCV7 in terms of post-primary series immunogenicity for the shared serotypes.^9–11^ Despite the availability of both PCV10 and PCV13 for several years, there have been no published studies to date directly comparing their post-primary series immunogenicity or impact on nasopharyngeal (NP) carriage.

The cost of PCVs is a major barrier to vaccine introduction in low-income to middle-income countries; therefore, investigation of alternative schedules with a reduced number of doses is of great importance. The uptake of PCV introduction in Asia has been particularly slow. Three schedules are currently in routine use around the world for PCV introduction: a 3+1 schedule (a three-dose primary series followed by a booster dose in the second year of life), a 3+0 schedule (a three-dose primary series without a booster dose) and a 2+1 schedule (a two-dose primary series followed by a booster dose in the second year of life). Data from periods of PCV7 shortage in the USA show high vaccine effectiveness of a two-dose primary series against IPD,^12 13^ and trial data of CRM_197_-conjugated PCVs show comparable immunogenicity following a two-dose or three-dose primary series, although antibody levels to serotypes 6B and 23F tend to be lower after two doses.^14 15^ Trials of PCV10 and PCV13 also support the use of a two-dose primary series. A trial of PCV10 in Europe directly comparing the immunogenicity of a two-dose and three-dose primary series showed a similar proportion of participants achieving protective antibody levels (≥0.2 µg/mL) for all 10 serotypes.^16^ In a trial of PCV13 in Mexico, over 93% of participants achieved protective antibody levels (≥0.35 µg/mL) for most of the 13 serotypes following two doses, with the exception of serotypes 6B and 23F.^17^ Four trials in Europe directly comparing PCV13 and PCV7 responses showed comparable immune responses between the vaccines following two doses.^18^

In developing countries, a 2+1 schedule with a booster dose in the first year of life may be advantageous. This modified schedule would likely increase compliance, would provide full immunisation closer to the peak incidence of pneumococcal disease and could enable the booster dose to coincide with measles vaccination. Alternatively, a further reduced PCV schedule with only two doses may be optimal for pneumococcal vaccination. Our previous trial in Fiji showed that protective antibody levels were reached for five of the seven serotypes following a single dose of PCV7 at 14 weeks of age.^15^ Furthermore, a booster dose of the 23-valent pneumococcal polysaccharide vaccine at 12 months of age was more immunogenic following a single dose primary series of PCV7 compared with a two-dose or three-dose primary series for four serotypes, and comparable for the other three serotypes.^19^ A trial of PCV9 from South Africa also showed that one dose at 6 weeks of age elicited a significant response for seven serotypes,^20^ and modelling data from the USA suggest that a single dose of PCV could prevent up to 62% of IPD.^21^ More recently, in the UK, where routine infant PCV vaccination has been in place for over 10 years, a 1+1 schedule of PCV13 was shown to elicit equivalent or superior post-booster responses compared with a 2+1 schedule for nine serotypes.^22^

Carriage of pneumococci in the nasopharynx is commonly a prerequisite for IPD and is the usual means of transmission of the bacteria. The herd effect of pneumococcal vaccination is mediated by the impact on NP carriage.^23^ Vaccination with PCVs generally results in a decrease in vaccine type (VT) pneumococcal carriage, which is most commonly observed after a booster dose and often accompanied by a compensatory increase in non-VT carriage.^23–27^ There have been few trials that evaluate the effect of different PCV schedules on carriage. A trial from the Netherlands showed that a two-dose primary series with or without a booster reduced VT carriage at 12 months of age compared with controls.^28^ VT carriage was further reduced at 18 months in the group that received the booster dose, compared with the group that did not receive the booster, although this difference did not persist at 24 months of age. Similarly, our trial in Fiji showed that a two-dose or three-dose primary series with or without a booster reduced VT carriage at 12 months of age compared with controls, but no difference was seen at 17 months of age ([name], personal communication).

It has been hypothesised that the protein D carrier in PCV10 may result in an impact on *H. influenzae* carriage. A recent review of the impact of protein D-containing PCVs on NTHi carriage concludes that any such impact is likely to be small and transient, although changes in the density of carriage are yet to be evaluated. Two large phase III trials (POET trial of an 11-valent PCV and COMPAS trial of PCV10) showed trends towards a reduction in NTHi carriage following a booster dose of PCV, along with a trial of PCV10 in toddlers in Kenya, but other trials conducted in Finland, the Netherlands and the Czech Republic showed no impact of PCV10 on NTHi carriage.^29^

This trial includes six infant vaccination schedules: four different PCV10 schedules (arm A, a 3+1 schedule at 2, 3, 4 and 9 months of age; arm B, a 3+0 schedule at 2, 3 and 4 months; arm C, a 2+1 schedule at 2, 4 and 9.5 months; and arm D, a two-dose schedule at 2 and 6 months); a 2+1 PCV13 schedule at 2, 4 and 9.5 months (arm E); and a control group that receives two doses of PCV10 at 18 and 24 months (arm F). In response to more recent interest in schedules with only one or two doses of PCV, which may be sufficient to maintain herd immunity at the population level, an additional control group is recruited at 18 months of age for comparison with the initial control group (arm G).

### Explanation for choice of comparators

There was no PCV licensed in Vietnam at the time the protocol was finalised in 2013. The inclusion of control groups that receive no infant doses of PCV is therefore justified. Control group participants recruited in infancy receive two doses of PCV10, at 18 and 24 months of age. Control group participants recruited at 18 months of age receive a single dose of PCV10 at 24 months of age. Intervention group participants receive at least two doses of PCV in the first year of life. All participants receive pneumococcal immunisation that is likely to be effective and is not otherwise available in Vietnam. The specific regimens to be evaluated are based on likely future global recommendations and to directly compare the two licensed PCVs.

Both PCV10 and PCV13 have been shown to be non-inferior to PCV7 for the serotypes common to both vaccines, and to have the potential to provide protection against the additional serotypes included.^9–11^ For both vaccines, the most common adverse reactions are redness at the injection site and irritability, which are common following administration of other vaccines. Other adverse reactions may include drowsiness; temporary loss of appetite; pain, redness or swelling at the injection site; and fever. Such reactions are usually temporary.

## Objectives

This trial has been designed to answer two independent questions concurrently, relating to the evaluation of different schedules incorporating PCV10 and the comparison of PCV10 and PCV13:What is the optimal schedule for provision of EPI vaccines with the incorporation of PCV10; andHow do the responses to vaccination with PCV10 or PCV13 compare?

The primary endpoint for both study questions is the post-primary series immunogenicity. For this endpoint, data from arms A and B are combined, as they receive an identical three-dose primary series (see table 1 for a detailed description of the trial arms). The primary analysis for each study question is to assess non-inferiority of the post-primary series immunogenicity (in terms of the proportion of participants achieving protective levels of serotype-specific IgG of ≥0.35 µg/mL), using arms A+B as the comparator (see below for details). Non-inferiority is assessed for each of the 10 serotypes in PCV10, and an overall conclusion of non-inferiority drawn if found for at least 7 of the 10 serotypes.

**Table 1 T1:** Schedule of enrolment, interventions and assessments

Age (months)	2	3	4	5	6	7	9	9.5	10	12	18	19	24
Enrolment													
Informed consent	X										X*		
Eligibility assessment	X										X*		
Allocation	X												
Interventions													
PCV10—group A	X	X	X				X						
PCV10—group B	X	X	X										
PCV10—group C	X		X					X					
PCV10—group D	X				X								
PCV13—group E	X		X					X					
PCV10—group F											X		X
PCV10—group G													X
Assessments													
Demographics	X										X*		
Household characteristics	X										X*		
Nasopharyngeal swab	X				X		X			X	X		X
Blood sample—group A	X†			X			X		X		X†		
Blood sample—group B				X	X		X†		X		X†		
Blood sample—group C				X	X†		X		X		X†		
Blood sample—group D		X			X	X	X†				X†		
Blood sample—group E		X†		X			X		X		X†		
Blood sample—group F											X	X	X
Blood sample—group G											X	X	X
General health	X	X	X	X	X	X	X	X	X	X	X	X	X

*Group G only. Any events occurring before 18 months do not apply to group G.

†Each participant provides only one of these blood samples (the last 50 participants per group enrolled into groups A–E provide this blood sample at 18 months; the remainder provide it at the other time point).

### What is the optimal schedule for provision of Expanded Program of Immunisation (EPI) vaccines with the incorporation of PCV10?

#### Primary objective

The primary objective is to compare a 2+1 schedule at 2, 4 and 9.5 months of age with a 3+1 schedule at 2, 3, 4 and 9 months of age. The primary hypothesis is that the proportion of participants with protective levels of antibody is non-inferior following a two-dose primary series (arm C) compared with a three-dose primary series (arms A+B). The schedules will also be compared in relation to the geometric mean concentrations (GMCs) of IgG and opsonophagocytosis post-primary series; the proportion of participants with protective levels of antibody, the GMCs of IgG and opsonophagocytosis post-booster; the memory B-cell responses; and the impact on nasopharyngeal (NP) carriage rates and density of bacteria of interest.

#### Key secondary objectives

To investigate an experimental two-dose schedule at 2 and 6 months of age (arm D), compared with a 3+1 schedule (arm A±B) and a 2+1 schedule (arm C); andTo assess the impact of a booster dose on NP carriage of pneumococcus and NTHi, comparing a 3+1 schedule (arm A) with a 3+0 schedule (arm B) and with unvaccinated controls (arm F).

### How do the responses to vaccination with PCV10 or PCV13 compare?

#### Primary objective

The primary objective is to compare a PCV13 schedule at 2, 4 and 9.5 months of age with a PCV10 schedule at 2, 3, 4 and 9 months of age. The primary hypothesis is that the proportion of participants with protective levels of antibody is non-inferior following a two-dose primary series of PCV13 (arm E) compared with a three-dose primary series of PCV10 (arms A+B). The schedules will also be compared in relation to the GMCs of IgG and opsonophagocytosis post-primary series; the proportion of participants with protective levels of antibody, the GMCs of IgG and opsonophagocytosis post-booster; the memory B-cell responses; and the impact on nasopharyngeal (NP) carriage rates and density of bacteria of interest.

#### Key secondary objectives

To compare PCV10 (arm C) and PCV13 (arm E) in a 2+1 schedule at 2, 4 and 9.5 months of age; andTo compare the responses to a single dose of PCV10 (arm D) and PCV13 (arm E).

### Additional objectives

Additional objectives relating to the second control group (arm G) are:To evaluate a single dose of PCV10 at 18 months of age, comparing serotype-specific antibody levels in arms F and G at 18, 19 and 24 months of age; andTo compare the immunogenicity and reactogenicity of *Infanrix-hexa* at 18 months of age in children who have received three doses of *Infanrix-hexa* or *Quinvaxem* in infancy (arm G).

### Trial design

The Vietnam Pneumococcal Project is a single-blind, open-label, randomised controlled phase II/III non-inferiority trial to investigate simplified childhood vaccination schedules that are more appropriate for developing country use. This is a seven-arm trial that includes six different infant vaccination schedules (arms A–F) and an additional control group (arm G) recruited at 18 months of age (table 1). Arm A receives PCV10 at 2, 3, 4 and 9 months of age (3+1); arm B receives PCV10 at 2, 3 and 4 months (3+0); arm C receives PCV10 at 2, 4 and 9.5 months (2+1); arm D receives PCV10 at 2 and 6 months (two-dose); arm E receives PCV13 at 2, 4 and 9.5 months (2+1); arm F receives two doses of PCV10 at 18 and 24 months; and arm G receives one dose of PCV10 at 24 months. Participants also receive *Infanrix-hexa* (DTP-Hib-HBV-IPV) instead of the routine EPI vaccine *Quinvaxem* (DTP-Hib-HBV): four doses for participants in arms A–F and one dose for arm G participants.

## Methods and analysis

### Study setting

PCV introduction in Asia has been slow, in part due to a lack of local or regional data on the effect of PCV. We selected the Southeast Asian country of Vietnam as the location for the trial as a country with a strong health system, a track record of conducting relevant clinical trials, and a Government with strong interest both in the trial and in introducing PCV in the near future. Furthermore, trial results from Vietnam are likely to be considered as applicable to other countries in the region. This is the first trial involving infants to take place within Ho Chi Minh City, the largest city in Vietnam. The trial is conducted in two districts, District 4 and District 7. Districts are divided into communes, each of which has a health centre that provides preventive health services including EPI immunisations, along with some primary healthcare services. The study is conducted in one commune health centre in each district, with participants drawn from the surrounding communes within that district.

### Eligibility criteria

#### Inclusion criteria

Subjects must meet all of the following inclusion criteria in order to be eligible to participate: aged between 2 months and 2 months plus 2 weeks (arms A–F) or aged between 18 months and 18 months plus 4 weeks (arm G); no significant maternal or perinatal history; born at or after 36 weeks’ gestation; written informed consent from the parent/legal guardian; lives within approximately 30 min of the commune health centre; anticipates living in the study area for the next 22 months (arms A–F) or 6 months (arm G); and received three doses of either *Quinvaxem* or *Infanrix-hexa* in infancy (arm G only).

#### Exclusion criteria

Subjects meeting any of the following exclusion criteria at baseline will be excluded from study participation: known allergy to any component of the vaccine; allergic or anaphylactic reaction to any previous vaccine; known immunodeficiency disorder; known HIV-infected mother; known thrombocytopenia or coagulation disorder; on immunosuppressive medication; administration or planned administration of any immunoglobulin or blood product since birth; severe birth defect requiring ongoing medical care; chronic or progressive disease; seizure disorder; history of invasive pneumococcal, meningococcal or *H. influenzae* type b diseases, or tetanus, measles, pertussis or diphtheria infections; receipt of any 2-month vaccines through the EPI programme (arms A–F), or receipt of PCV (arm G); or family plans on giving the infant *Quinvaxem* (arms A–F).

### Interventions

#### PCV schedules

Eligible participants recruited in infancy are randomised to one of six different vaccination schedules (table 1). Participants randomised to arms A–D receive PCV10 in a 3+1 schedule at 2, 3, 4 and 9 months of age; a 3+0 schedule at 2, 3 and 4 months of age; a 2+1 schedule at 2, 4 and 9.5 months of age; or a two-dose schedule at 2 and 6 months of age, respectively. Participants randomised to arm E receive PCV13 in a 2+1 schedule at 2, 4 and 9.5 months of age. Control group participants receive PCV10 at 18 and 24 months of age if randomised to arm F, or PCV10 at 24 months of age if recruited to arm G at 18 months of age. PCV is administered by intramuscular injection into the anterolateral thigh in children less than 18 months old and in the deltoid muscle of the arm in children aged 18 months and over. All vaccinations are performed by nurses specifically trained in infant vaccine administration.

#### PCV10

PCV10 (*Synflorix*) is a 10-valent pneumococcal polysaccharide conjugate vaccine using protein D (a highly conserved surface protein from NTHi) as the main carrier protein. PCV10 is presented as a turbid white suspension in a two-dose phial. One dose consists of 0.5 mL of the liquid vaccine, containing 1 µg of pneumococcal polysaccharide from serotypes 1, 5, 6B, 7F, 9V, 14 and 23F and 3 µg of pneumococcal polysaccharide from serotypes 4, 18C and 19F. Serotypes 1, 4, 5, 6B, 7F, 9V, 14 and 23F are conjugated to protein D; serotype 18C is conjugated to tetanus toxoid carrier protein; and serotype 19F is conjugated to diphtheria toxoid carrier protein.

#### PCV13

PCV13 (*Prevnar-13*) is a 13-valent pneumococcal polysaccharide conjugate vaccine using non-toxic diphtheria CRM_197_ carrier protein. PCV13 is presented as a 0.5 mL suspension in a single-dose pre-filled syringe. One dose contains approximately 2.2 µg of pneumococcal polysaccharide from serotypes 1, 3, 4, 5, 6A, 7F, 9V, 14, 18C, 19A, 19F and 23F and 4.4 µg of pneumococcal polysaccharide from serotype 6B.

#### Criteria for discontinuing or modifying allocated interventions

There is no modification of doses for participants in this study. If a participant has an allergic or anaphylactic response to vaccination, they will be withdrawn from the study. Participants may also be withdrawn voluntarily by the parent/legal guardian at any time, or by the study staff if they refuse any further study procedures or develop any of the exclusion criteria during the course of the study.

#### Strategies to improve and monitor adherence

Scheduled visit dates are noted on a health record card kept by the parent. If a participant does not attend a scheduled visit, a reminder phone call is made from the study clinic. If the participant cannot be contacted directly, their local commune health centre is contacted for further follow-up by phone or by home visit.

#### Relevant concomitant care

Participants receive *Infanrix-hexa*, which is only available on the private market, instead of the routine EPI vaccine *Quinvaxem*. Participants in arms A–F receive four doses in one of the following schedules: 2, 3, 4 and 19 months (arms A and B); 2, 4, 9.5 and 19 months (arms C and E); 2, 4, 6 and 19 months (arm D); or 2, 3, 4 and 18 months (arm F); and participants in arm G receive one dose at 18 months of age. The routine EPI measles and measles–rubella immunisations are also provided during the course of the study: measles at 9 months of age and measles–rubella at 18 (arms A–E) or 19 (arms F–G) months of age. Participants allocated to one of the 2+1 vaccination schedules (arms C and E) receive measles at 9 months of age and receive PCV and *Infanrix-hexa* 2 weeks later. For visits with two vaccinations, the vaccines are administered in different limbs. Other vaccinations are permitted in this study with a 2-week interval from study vaccines, with the exception of *Quinvaxem* in arms A–F. Other medications are also permitted, with the exception of immunosuppressive medication and medications listed as contraindicated to the study vaccines.

### Outcomes

#### Primary outcome measure

The primary outcome measure is the concentration of serotype-specific IgG for the 10 serotypes common to both PCV10 and PCV13, assessed 4 weeks post-primary series and measured using a modified third-generation standardised ELISA.^30^ Primary comparisons between arms are made in terms of the proportion of children with antibody concentration ≥0.35 µg/mL for individual serotypes. The cut-off of 0.35 µg/mL was determined as a result of a pooled analysis of data from efficacy trials^31^ and is used as the basis for non-inferiority assessments for the approval of new PCVs.^32–34^

#### Secondary immunogenicity outcome measures

Serotype-specific IgG antibody concentrations for all PCV13 serotypes are measured by ELISA from all blood samples (table 1) and are summarised in terms of both the proportion of children with antibody concentration ≥0.35 µg/mL and the GMC.Opsonisation indices (OIs) for all PCV13 serotypes are measured by opsonophagocytic assay (OPA)^35^ for 100 participants per intervention group (arms A–E) 4 weeks post-primary series and 4 weeks post-booster, and are summarised in terms of the proportion of participants with OI ≥8 and the geometric mean titre.Polysaccharide-specific memory B cells for serotypes 1, 5, 6B, 14, 18C, 19A and 23F are enumerated by ELISPOT^35^ for 50 participants per intervention group (arms A–E) post-booster and at 18 months of age, and for 100 participants per control group (arms F and G) at 18 and 24 months of age. The results are summarised as the median number of antibody-secreting cells.

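### Table 1 and the outcomes text contradict each other on the post-booster blood draw in arms C and E: about 2 weeks after the booster in one, 4 weeks in the other

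*Protocol article*

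**What the plan says.** Under Secondary immunogenicity outcome measures, the Protocol article places opsonophagocytic testing "for 100 participants per intervention group (arms A–E) 4 weeks post-primary series and 4 weeks post-booster". It makes no exception for any arm. The same section says IgG is measured on all the blood samples in Table 1, and gives no interval for the post-booster memory B-cell sample.

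The booster ages are stated under Trial design: "Arm A receives PCV10 at 2, 3, 4 and 9 months of age (3+1"), "arm C receives PCV10 at 2, 4 and 9.5 months (2+1") and "arm E receives PCV13 at 2, 4 and 9.5 months (2+1"). Relevant concomitant care explains the half-month offset: arms C and E "receive measles at 9 months of age and receive PCV and *Infanrix-hexa* 2 weeks later".

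In Table 1 (Objectives), the row "Blood sample—group A" has draws at 5, 9 and 10 months, plus one at either 2 or 18 months. The row "Blood sample—group C" has draws at 5, 9 and 10 months, plus one at either 6 or 18 months. Arm E also has draws at 5, 9 and 10 months. In all three arms the 10-month draw is the first after the booster. The table has a 9.5-month column and no 10.5-month column.

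**The concern.** For arms C and E, a 9.5-month booster, a 10-month draw and a 4-week interval cannot all be true. A reader cannot tell from the article when the post-booster sample is taken in the two 2+1 arms.

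This matters because post-booster antibody proportions, IgG concentrations and opsonophagocytosis are named comparisons under the primary objective of each study question: the PCV10 2+1 schedule against 3+1, and PCV13 2+1 against PCV10 3+1. If Table 1 is followed, arm A is sampled at about twice the interval since booster of arms C and E. Any difference, or absence of one, would then reflect both the schedule (and for arm E the vaccine) and where each arm stands on its post-booster antibody curve.

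**Working it through.** **Inputs.** All are nominal ages from Table 1, with the booster ages confirmed under Trial design. One month is 30.4375 / 7 = 4.35 weeks.

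**Formula.** Interval in weeks = (age at draw − age at dose) × 4.35.

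**The stated figure first (4 weeks).**
- Arm A: (10 − 9) × 4.35 = 4.35 weeks. This agrees.
- Arms C and E: (10 − 9.5) × 4.35 = 2.17 weeks. This does not agree.
- Arms C and E, taking the booster at 9 months plus exactly 2 weeks: 4.35 − 2 = 2.35 weeks. This does not agree either.

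The gap between arm A and arms C and E is therefore about 2.0 to 2.2 weeks.

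**Is this how the table treats post-dose draws in general?** No. The other draws that follow a dose are one month later:

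| Dose to draw (months) | Arms | Interval |
|---|---|---|
| 4 to 5 | A, B, C, E | 4.35 weeks |
| 2 to 3 | D, E | 4.35 weeks |
| 6 to 7 | D | 4.35 weeks |
| 18 to 19 | F | 4.35 weeks |
| 9 to 10 | A | 4.35 weeks |
| 9.5 to 10 | C, E | 2.17 weeks |

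The post-booster draw in C and E is the only exception.

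**Where a 4-week draw would fall.** In C and E: 9.5 + 4/4.35 = 10.42 months, or 9 + 6/4.35 = 10.38 months with the 2-week definition. In arm A: 9 + 4/4.35 = 9.92 months. A table that distinguishes 9 from 9.5 would be expected to show the C and E draw at about 10.5.

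**Can the planned analysis absorb the difference?** Statistical methods describes the booster analysis as analysis of covariance on the pre-booster level. Under Table 1, time since booster is almost wholly determined by arm when C or E is compared with A, so no covariate can separate the two. The covariate is itself timed unequally: the 9-month sample is at the booster age in arm A but about 2.2 weeks before the booster in C and E.

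**Size of any bias.** This needs the change in antibody between about 2 and 4 weeks after a booster. The article gives nothing from which to derive it, so no figure is offered.

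**The case against.** The best defence is that Table 1 ages are nominal. Infants enrol anywhere from 2 months to 2 months plus 2 weeks, a range as wide as the gap at issue, and visit windows may sit in the full protocol, which is not shown. The 10-month column could then label a visit that in C and E takes place at about 10.4 months. This cannot be excluded, but the table argues against it. It uses a separate half-month column where half a month matters, every other post-dose draw follows by one month, and unboosted arm B also has a 10-month draw, so the column is not defined purely by time since booster. Even if the label is nominal, Table 1 needs correcting.

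Second, the 4-week wording is attached only to opsonophagocytosis, and it names arms A to E although B and D receive no booster. It is loose wording, and the direct contradiction is confined to that assay. This stands. The IgG comparisons are exposed because their samples are those of Table 1, not because the text promises 4 weeks for them.

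Third, the opsonophagocytic and memory B-cell data are to be analysed descriptively, so the formal analysis exposed is the secondary covariance analysis of the booster response. This also stands, and limits the severity.

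A reader might infer that C and E are in fact bled 2 weeks after the booster and that the schedule comparisons are therefore confounded. The documents do not establish that. They give two incompatible schedules, and confounding follows only under Table 1. Nor do they support a numerical bias.

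**Conclusion.** The contradiction is established: about 2.2 weeks (2.17 to 2.35) from Table 1 against a stated 4 weeks in arms C and E, with arm A consistent at 4.35 weeks. Confounding with time since booster is conditional on Table 1 being the operative schedule. In that case it affects the secondary post-booster IgG comparisons of C with A and E with A, and the descriptive opsonophagocytic and B-cell contrasts between those arms. Adjustment for the pre-booster level would not cure it, and its size and direction are unknown.

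A reader might extend this to the trial's main conclusions, but that is not supported. The primary endpoint is measured at 5 months, one month after the 4-month dose in arms A, B, C and E, so the non-inferiority tests and the power are untouched. C versus E shares booster and draw ages and stays time-matched. The point is moderate: wrong as written, and confined to secondary outcomes.

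**What to change.** Reconcile Table 1 with Secondary immunogenicity outcome measures, and state the intended interval from booster to post-booster draw for each boosted arm and each assay.

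- **If 4 weeks is intended:** show the C and E draw in Table 1 at 4 weeks after the 9.5-month dose (about 10.5 months), leaving arm A at 10 months. If draws already follow this, only the table changes. If not, one existing visit moves by about 2 weeks in two arms, with no added draws or assays.
- **If draws are, or were, taken at 10 months:** correct the 4-week wording for C and E, report post-booster C versus A and E versus A as not matched on time since booster, and present C versus E as the time-matched comparison. This costs wording only.

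The article does not say whether these samples have already been collected, so the sponsor must establish which case applies. Neither option alters a dose or a vaccination age.
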